**Relative exclusion criteria**		
	Acute IBD^d^ flares	Acute flares involve a burden of stress and anxiety, which might lead to false-positive results in cognitive testing. Patients will be informed of the possibility of inclusion, and if they agree, testing will be performed after the acute flare is over.
	Age over 70 years	Patients aged over 70 years might have age-related cognitive impairment, which might interfere with the study results.

^a^AD: Alzheimer’s disease.

^b^Hcy: homocysteine.

^c^MCI: mild cognitive impairment.

^d^IBD: inflammatory bowel disease.

### Study Timeline

Patients will be recruited based on the inclusion and exclusion criteria. The recruitment moment will be called “baseline.” Follow-up will be performed at 12, 24, and 36 months. A systematization of the procedures is presented in Table 4.

**Table 4 table4:** Study timeline.

Objective	Timeline			
	Baseline	12-month follow-up	24-month follow-up	36-month follow-up
Eligibility assessment	X^a^	—^b^	—	—
Signing of informed consent form	X	—	—	—
Exclusion and inclusion criteria reassurance	X	X	X	X
Demographics	X	—	—	—
Relationship status	X	—	—	—
Short cognitive and affective questionnaire	X	X	X	X
Physical examination	X	X	X	X
Medication assessment	X	X	X	X
Medical history assessment	X	—	—	—
Collection of blood sample and storage	X	—	—	—
Detailed risk factor questionnaire	X	—	—	—
Clinical disease activity score	X	X	X	X
Depression, stress, and anxiety screening	X	X		
COVID-19 questionnaire	X	—	—	—
Quality-of-life questionnaire	X	X	X	X
MOCA^c^	X	X	X	X
MIS^d^	X	X	X	X
TMT^e^-A	X	—	—	X
TMT-B	X	—	—	X
DSST^f^	X	—	—	X
FDST^g^	X	—	—	X
BDST^h^	X	—	—	X
ADL^i^ questionnaires	X	X	X	X
IADL^j^	X	X	X	X

^a^X: applicable.

^b^—: not applicable.

^c^MOCA: Montreal Cognitive Assessment.

^d^MIS: memory impairment score.

^e^TMT: Trail Making Test.

^f^DSST: Digit Symbol Substitution Test.

^g^FDST: forward digit span testing.

^h^BDST: backward digit span testing.

^i^ADL: activities of daily living.

^j^IADL: Instrumental Activities of Daily Living.

### Procedures and Examinations

Clinical procedures and examinations will be performed in a silent room so there is no disturbance to both examiner and participant. Participants will receive information about each test that will be conducted. The scales and questionnaires used in the study are listed in Table 5.

**Table 5 table5:** Scales used in the study.

Objective	Scales
Assessment of IBD^a^ severity	HBI^b^ for patients with CD^c^ and SCCAI^d^ for patients with UC^e^
Assessment of quality of life	Romanian WHOQOL-BREF^f^ questionnaire
Assessment of depression, anxiety, and stress	Romanian DASS^g^-21
Cognitive assessment	Romanian MOCA^h^ 7.1, TMT^i^-A and TMT-B, backward digit testing, forward digit testing, DSST^j^
Assessment of COVID-19	Short COVID-19 questionnaire
Assessment of ADL^k^	IADL^l^ scale, Katz ADL scale

^a^IBD: inflammatory bowel disease.

^b^HBI: Harvey-Bradshaw Index.

^c^CD: Crohn’s disease.

^d^SCCAI: Simple Clinical Colitis Activity Index.

^e^UC: ulcerative colitis.

^f^WHOQOL-BREF: World Health Organization Quality of Life Brief Version.

^g^DASS: Depression-Anxiety-Stress Scale.

^h^MOCA: Montreal Cognitive Assessment.

^i^TMT: Trail Making Test.

^j^DSST: Digit Symbol Substitution Test.

^k^ADL: activities of daily living.

^l^IADL: Instrumental Activities of Daily Living.

The Montreal Cognitive Assessment (MOCA) 7.1 scale includes the Trail Making Test (TMT), drawing, long-term memory testing, verbal fluency tests, short-term memory recall testing, calculus, and spatial and temporal orientation questions. The maximum score obtained is 30 points. The normal range is ≥26 points. An additional point is given to patients who have an education level of ≤12 years.

The memory impairment score (MIS) is derived from the MOCA scale. The maximum score is 15 points. It derives from the short-term memory recall test. Subjects have to recall 5 words to gain points. If they recall the words spontaneously, 3 points are awarded for each word. If any clue is provided, 2 points are awarded if the word is recalled. If variants are provided, 1 point is awarded if the word is recalled. No point is awarded if the word is not recalled.

The TMT involves the subject drawing a trail between 2 points, with the entire operation being timed. It has 2 different parts, TMT-A and TMT-B. TMT-A involves drawing a continuous line between numbers. TMT-B involves drawing a continuous line, alternating letters and numbers. An example of the test is provided before each part. TMT-A has a maximum time of 100 seconds, and 101 seconds means the subject has failed the test. TMT-B has a maximum time of 300 seconds, and 301 seconds means the subject has failed the test.

The Digit Symbol Substitution Test (DSST) involves the subject changing some numbers to symbols as specified in the legend of the test. A training zone is first created. If the training is completed, the subject is given 90 seconds to complete as many substitutions as possible. Correct and incorrect answers are counted.

In forward digit span testing (FDST) and backward digit span testing (BDST), the subject must recall the numbers provided by the examiner in forward order and then in backward order. FDST involves strings of numbers ranging from 2 to 8 numbers, and BDST involves strings of numbers ranging from 2 numbers to 7 numbers. Each string has 2 different variants, and the subject must make a maximum of 1 mistake in these variants, otherwise the test ends.

The Depression-Anxiety-Stress Scale (DASS) is a scale that includes 21 questions split into 3 categories (depression, stress, and anxiety), with 7 questions per category, the questions being interleaved. Each question has a score from 0 to 3, and the result is multiplied by 2.

The Harvey-Bradshaw Index (HBI) and the Simple Clinical Colitis Activity Index (SCCAI) are used for screening the subject. In this study, they are part of the inclusion criteria.

The quality-of-life instruments available in Romania are limited; therefore, the World Health Organization Quality of Life Brief Version (WHOQOL-BREF) will be used in order to determine the quality of life of our participants. The Instrumental Activities of Daily Living (IADL) is an 8-item scale that includes some instrumental daily activities, and it is a useful and essential tool for differentiating MCI from dementia. The Katzl ADL scale is a 6-item scale that includes casual daily activities and is also a useful and essential tool for differentiating MCI from dementia.

A blood sample will be obtained from each participant.

### Outcomes

The first to be mentioned are demographic variables, which will be useful for stratifying our participants; the expected answers are presented in Table 6.

**Table 6 table6:** Demographic variables.

Demographic characteristics	Expected answers
Education level	Absolute number of years
Current living environment	Rural, urban <10,000 inhabitants, urban 10,000-49,999 inhabitants, urban 50,000-99,999 inhabitants, urban >100,000 inhabitants
Marital status	Married, single, cohabitation, divorced, polygamy, widowed
Employment	Employed full-time, employed part-time, freelancer, retired, student, trainee
Toxic working environment	Yes, no, do not know
Night shifts	Yes, no
Financial status	Enough for a living and saving, enough for a living but not saving, not enough for a living
Monthly wage (average per family member)	<1500 lei (<USD 316.31), 1500-2500 lei (USD 316.31-527.18), 2500-3500 lei (USD 527.18-738.05), 3500-4500 lei (USD 738.05-948.93), >4500 lei (>USD 948.93)

The relationship status is important for affective mood but also for cognitive functioning; therefore, 3 questions will be answered by the participants, listed in Table 7.

**Table 7 table7:** Current and past relationship data.

Question	Expected responses
Married before diagnosis of IBD^a^	Yes, no, not available
Relationship destabilization due to the disease	Yes, and it caused a broken relationship or divorce; yes, but it did not cause a broken relationship or divorce; no
Helped with the disease by the life partner	Yes, no, not available

^a^IBD: inflammatory bowel disease.

A short cognitive assessment will be performed in order to accommodate the participants in the subsequent questionnaires and tests. Questions are mentioned in Table 8.

**Table 8 table8:** Short cognitive (long-term memory) and affective assessment.

Question	Expected responses
Trouble with memory in the past month	Yes, occasionally, no
Changes in personality	Yes, no
Difficulties in handling daily activities due to memory changes	Yes, no
Family history of dementia	Yes, AD^a^; yes, other dementia; no; do not know
Current president of Romania	Correct or incorrect answer
The year of the Great Union in Romania	Correct or incorrect answer
Naming a pencil	Correct or incorrect answer
Naming a medical coat	Correct or incorrect answer
Naming a clock	Correct or incorrect answer

^a^AD: Alzheimer’s disease.

A short clinical examination will be performed. A full history of IBD will be taken. Variables obtained are mentioned in Table 9. The HBI and SCCAI will be the clinical disease activity scales used in the study, as mentioned in Table 10. Risk factor assessment will also be performed (Table 11).

**Table 9 table9:** Physical examination and past medical history.

Variables		Expected responses
**Physical examination**		
	Blood pressure	Value (mmHg)
	Pulse	Absolute number (beats/minute)
	Respiratory rate	Absolute number (respirations/minute)
	Peripheric oxygenation percentage	Value (%)
Medication assessment		All concomitant medications used (international common names and dosing and posology)
**IBD^a^ history assessment**		
	Year of diagnosis	Absolute number
	Montreal classification	A-L-B^b^ for CD^c^ patients, E-S^d^ for UC^e^ patients
	Family history of IBD	Yes, no, do not know
	Number of flares in the past 12 months	Absolute number
	Number of flares since diagnosis	Absolute number
	Number of hospitalizations for flares in the past 12 months	Absolute number
	History of corticosteroid dependency	Yes, no
	Duration of corticosteroid dependency (if the above answer is yes)	Absolute number (months)
	Current medication	Name, dose, duration
	Past medication	Name, dose, duration
	Complications	Enumeration

^a^IBD: inflammatory bowel disease.

^b^A-L-B: onset (A), disease location (L), and disease behavior (B).

^c^CD: Crohn’s disease.

^d^E-S: extent (E) and severity (S).

^e^UC: ulcerative colitis.

**Table 10 table10:** Clinical disease activity score assessment.

Scales and items			Scoring (points in parentheses)
**HBI^a^ (0-4 points=remission; 5-7 points=mild disease; 8-16 points=moderate disease; >16 points=severe disease)**			
	General health	Very well (0), slightly below par (1), poor (2), very poor (3), terrible (4)	
	Abdominal pain	None (0), mild (1), moderate (2), severe (2)	
	Liquid or soft stools on the previous day	Absolute number (1 point for each)	
	Abdominal mass	None (0), dubious (1), definite (2), definite tender (3)	
	Complications	Arthralgia (1), uveitis (1), erythema nodosum (1), aphthous ulcer (1), pyoderma gangrenosum (1), anal fissure (1), new fistula (1), abscess (1)	
**SCCAI^b^ (0-20 points; ≥5=active disease)**			
	Bowel frequency	0-3 stools (0), 4-6 stools (1), 7-9 (stools 2), >9 stools (3)	
	Bowel frequency (night)	0 stools (0), 1-3 stools (1), 4-6 stools (2)	
	Urgency defecation	No urgency (0), hurry (1), immediately (2), incontinence (3)	
	Blood in stool	No blood (0p, traces (1), occasionally frank (2), usually frank (3)	
	General health	Very well (0), slightly below par (1), poor (2), very poor (3), terrible (4)	
	Extracolonic manifestations	No feature (0), 1 feature (1), 2 features (2), 3 features (3), 4 features (4), 5 features (5)	

^a^HBI: Harvey-Bradshaw Index.

^b^SCCAI: Simple Clinical Colitis Activity Index.

**Table 11 table11:** Risk factor questionnaire.

Detailed risk factor questionnaire	Expected responses
Active smoker status	Yes, no, ex-smoker
Number of smoking years	Absolute number
Number of abstinence years	Absolute number
Daily number of cigarettes	Absolute number
Alcohol drinking rate	Daily, 3-5 times per week, 1-2 times per week, rarer, no drinking, other options (to be mentioned)
30 minutes of physical activity	Daily, 5 times per week, rarer, no physical activity, other frequency (to be mentioned)
Dietary trend	Nonspecific diet, vegetarian, vegan, flexitarian, colitis regimen, other (to be mentioned)
Number of sleeping hours per day (24 hours)	Absolute number
Daytime tiredness	Yes, no
Troubles with maintaining sleep	Yes, no
Troubles with falling asleep	Yes, no

A cognitive assessment must always be preceded by a screening of depression, anxiety, and stress because this may falsely create a diagnosis of cognitive dysfunction. Scales and their interpretations can be seen in Table 12.

**Table 12 table12:** Depression, anxiety, and stress screening; COVID-19 impact; current quality of life; and ADL^a^ assessment.

Scales and items			Expected responses
DASS^b^-21 scale (7 items each for depression, anxiety, and stress)			Depression (0-9, 10-13, 14-20, 21-27, ≥28 points), anxiety (0-7, 8-9, 10-14, 15-19, ≥20 points), stress (0-14, 15-18, 19-25, 26-33, ≥34 points)

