**Methods:**

A case-control study will be conducted on at least 100 patients diagnosed with IBD, matched with 100 healthy individual controls. The matching will include sex, age, and education. Patients will be fully examined, and a full interview and a neurological and cognitive examination will be performed. The primary clinical outcomes will be cognitive test scores (Montreal Cognitive Assessment, Trail Making Test, Digit Symbol Substitution Test, forward and backward digit span testing). Depression, stress, and anxiety screening will also be performed. Blood samples from all participants will be collected, and aliquots will be immediately stored in a biobank. Primary laboratory outcomes will include serum levels of presumed cognitive dysfunction blood biomarkers SAA, Hcy, S100B, and BDNF. Follow-up will be performed at 12, 24, 36, and 48 months.

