**Results:**

Data collection started in December 2021 and is ongoing. So far, 53 patients with IBD have been recruited and 50 HC matched. Data collection should end in January 2030. Intermediary analysis will be performed in April 2024. We expect patients with IBD to have lower scores on cognitive testing and a positive correlation between disease length and cognitive impairment level. In addition, the levels of stress, anxiety, and depression should be higher in the IBD group. The serum levels of the 4 biomarkers could correlate or anticorrelate with cognitive scores and serve as predictive factors for MCI or dementia development. A higher level of education, a younger age, the absence of malabsorption, and good disease control might serve as protectors against MCI.

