**48-month follow-up**			
	MOCA	0-30 points: executive function (0-5 points), naming (0-3 points), memory (0-5 points), attention (0-6 points), calculus (0-3 points), language (0-3 points), orientation (0-6 points), abstractization (0-2 points)	
	MIS	0-15 points	
	BDST	0-14 points	
	FDST	0-16 points	
	TMT-A	0-100 seconds (101 seconds means failed test)	
	TMT-B	0-300 seconds (301 seconds means failed test)	
	DSST	Absolute number of correct answers (maximum 90 correct answers), absolute number of incorrect answers (maximum 90 incorrect answers)	

^a^MOCA: Montreal Cognitive Assessment.

^b^MIS: memory impairment score.

^c^BDST: backward digit span testing.

^d^FDST: forward digit span testing.

^e^TMT: Trail Making Test.

^f^DSST: Digit Symbol Substitution Test.

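### Mood screening is required before every cognitive assessment, but Table 4 marks it only at baseline and 12 months while MOCA continues at later visits

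*Protocol article*

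**What the plan says.** In the Outcomes section, the text that introduces Table 12 sets a rule: "A cognitive assessment must always be preceded by a screening of depression, anxiety, and stress". The same sentence gives the reason, which is that mood symptoms can lead to a false finding of impaired cognition. Table 5 names the Romanian DASS-21 as the instrument, under "Assessment of depression, anxiety, and stress".

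Table 4 (Study Timeline) has a row for "Depression, stress, and anxiety screening". It is marked at baseline and 12 months, and its 24- and 36-month cells are empty. The MOCA and memory impairment score rows are marked at all four visits. TMT-A, TMT-B, DSST and both digit spans are marked at baseline and 36 months.

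The length of follow-up is stated in two ways. Study Timeline says "Follow-up will be performed at 12, 24, and 36 months", and the abstract says "Follow-up will be performed at 12, 24, 36, and 48 months". Table 13 has a block headed "48-month follow-up" that contains MOCA, the memory impairment score and the whole remaining battery. Table 4 has no column for that visit.

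The abstract also states the expectation that "the levels of stress, anxiety, and depression should be higher in the IBD group".

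**The concern.** The rule admits no exceptions, and the schedule does not meet it. The visits without marked screening are the later ones. They feed the secondary objective on MCI progression (Table 1) and part of the 12-to-48-month span over which the Discussion summary describes the link between biomarkers and cognition.

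The protocol supplies the reasons why this matters. It says that mood can produce a false cognitive diagnosis. It uses a similar argument in Table 3 to postpone testing during flares, which occur only in the IBD group. It also expects worse mood in IBD than in controls. On those premises, a mood effect on later cognitive scores would tend to favour the study hypothesis. Without a DASS-21 score from the same visit, a reader could not tell whether a lower MOCA at month 24 or 36 reflects current mood or cognitive decline. If the form was not given, no analysis plan can recover the data.

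**Working it through.** No figure in the plan depends on this point. The sample-size calculation concerns a mean MOCA difference and is untouched. The check sets the schedule rows side by side.

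| Visit | MOCA and memory impairment score | TMT, DSST, digit spans | Mood screening |
|---|---|---|---|
| Baseline | marked | marked | marked |
| 12 months | marked | dash | marked |
| 24 months | marked | dash | blank |
| 36 months | marked | marked in Table 4; not listed in Table 13 | blank |
| 48 months (abstract, Table 13) | listed in Table 13 | listed in Table 13 | no column in Table 4 |

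1. MOCA visits in Table 4: 4. Visits with screening marked: 2. Without: 4 − 2 = 2, so 2 of 4 overall. Baseline is screened, so this is 2 of the 3 follow-up visits.
2. With month 48 added: 5 MOCA visits, 2 with screening marked, 5 − 2 = 3 without. That is 3 of 5 overall and 3 of the 4 follow-up visits.
3. The full battery is repeated once, at 36 months by Table 4 or at 48 months by Table 13. Neither visit has screening scheduled, so the only repeat of TMT, DSST and digit span lacks it whichever table is right.

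Next, does anything else in the schedule do the same job?

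- The short cognitive and affective questionnaire is marked at every Table 4 visit. Its items (Table 8) cover memory complaints, personality change, daily activities, family history, general knowledge and naming. None asks about depression, anxiety or stress.
- WHOQOL-BREF is marked at every Table 4 visit and has a psychological domain, but that is a quality-of-life score and not a screen of the three mood scales.
- The recheck of inclusion and exclusion criteria at each Table 4 visit concerns listed conditions, such as psychiatric disorders, and not current symptom severity.

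None of these replaces DASS-21, and no other part of the article schedules it after 12 months.

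**The case against.** The strongest reply is that Table 4 is silent and does not rule screening out. It defines a dash for not applicable, and the mood row has two empty cells where a dash could have stood. A merged cell, a typesetting loss or a fault in reading the table would look the same, and a rule that says always makes an accidental omission plausible. This stands in part: a reader might infer that the plan has decided to stop mood screening after month 12, and the documents do not establish that. It does not remove the need to reconcile the text with the table, because staff who work from Table 4 have no instruction to give the form at those visits.

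A second reply is that the effect on progression is limited. A stable mood difference between the groups largely cancels in within-person change, and the baseline and 12-month DASS-21 scores are available for adjustment. Psychiatric disorders are also excluded at entry. This is fair. What the gap leaves unseen is change in mood after month 12, and the entry exclusion does not prevent new symptoms during follow-up.

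A third reply is that covariates and sensitivity analyses are usually left to the analysis plan. That holds for the modelling, but the visit schedule is printed here and conflicts with the text beside it.

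Finally, a reader might infer that concurrent mood must be entered as a time-varying covariate. The documents do not support making this mandatory. The Introduction describes mood disorders as something that may promote cognitive impairment, and the Conclusion describes them as a possible prodrome. If mood lies on the pathway, such adjustment could remove part of the effect under study.

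**Conclusion.** The contradiction holds. As printed, 2 of 3 follow-up MOCA visits, or 3 of 4 if month 48 is held, have cognitive testing without the screening that the protocol says must come first. This count needs no assumption beyond following Table 4 as it stands.

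The consequence is narrower than it may appear. Later MCI results are open to an effect of current mood that could not be checked. A reader might infer that they are biased, or try to put a size on a false excess of MCI in IBD. The documents give neither the frequency of mood symptoms in the two groups nor their effect on MOCA, so neither step is supported. A cross-sectional excess would also not measure the cost of missing the later screening, which depends on differential change in mood after month 12. The primary baseline comparisons, and the first phase that ends at 12 months, are unaffected. The point is worth correcting, for the sake of the secondary progression objective.

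**What to change.** Reconcile the Outcomes text, Table 4 and Table 13:

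- Fill the two blank cells in the mood-screening row of Table 4, so that DASS-21 is marked at every visit with MOCA and is given before the cognitive tests.
- Settle whether a 48-month visit takes place. If it does, give it a column in Table 4 with DASS-21 marked, and make Tables 4 and 13 agree on when the full battery is repeated.
- Report MCI results from the later visits with and without participants above the DASS-21 cut-offs, as a sensitivity analysis. Name in advance which of the Table 12 bands counts as above the cut-off.

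The cost is a 21-item form that is already in use, given at two or three more visits per participant, which takes a few minutes each time. Data collection started in December 2021 and is planned to run to January 2030, so most later visits could still be covered. Participants enrolled at the start reach month 24 in December 2023, and any score not collected at a visit is lost.

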**COVID-19 impact questionnaire**			
	Vaccination status	Yes, no	
	COVID-19 vaccine (if the above answer is yes)	BNT162b2, NJ-78436735 (Ad26.COV2.S), AZD1222 (ChAdOx1), mRNA^c^-1273, other (mentioned in the questionnaire)	
	Number of doses	Absolute number	
	History of infection	Yes, no, do not know	
	WHOQOL-BREF^d^	Social relationships (4-20 points), environment (4-20 points), physical health (4-20 points), psychological (4-20 points)	
